### Supervised exercise training programme

The exercise training protocol will consist of a 10–15-minute warm-up, followed up by a 45–50-minute combination of strength and circuit training. The exercise training programme is based on national guidelines for cardiac rehabilitation [28]. The warm-up will be based on either bicycling, with a focus on using the forefoot when pedalling, or walking in different variations, i.e. walking on toes, heels, walking sideways, walking lunges and walking at different paces. In strengthening the large muscle groups, there will be a primary focus on the leg muscles. The strength exercises for the upper body will primarily be performed as an intermission, in the exercise for the lower body. Different exercise equipment will be used to create resistance in the exercise training, i.e. elastic bands, body bars, dumb bells, and strength-training machines. The exercise will vary from 1 × 15, 2 × 15, and 3 × 10 repetitions, based on low to moderate intensity of 40–60% of the maximum muscle strength [28]. The circuit training will primarily be based on activity for the lower limbs, i.e. walking and running at different paces and variations, walking combined with an exercise, i.e. high knee lifts, kick backs, calf raises, and different relay races in teams. The circuit training will also involve interval training, of varying lengths, depending on both the different exercises and the patients’ individual limits due to lower limb pain. Two of the sessions will be based on using and practising pole striding at a nearby outdoor training park. In addition to the physical activity component, the programme will also contain components of health education for improving the self-efficacy of physical activity in the patients and therefore seek to affect health behaviour. Five of the sessions will contain 10–15 minutes of health education, which will include the use of tools developed by Steno Diabetes Center, Copenhagen, Denmark. These tools were developed for supporting patients in making long-term health-related changes, and for the use of health professionals in health education for patients with chronic illness [29]. Furthermore, the health education will contain motivational, group-based dialogue with the patients about their health behaviour and ability to participate in physical activity in their own neighbourhood. There will also be motivational conversations concerning the patients’ daily use of and achievements with the pedometer and logbook handed out to each patient at the start of the intervention.

### Education in groups and individual consultation

The aim of the intervention is to provide emotional support, improve coping skills, and to respond to physical symptoms. Education and information about the disease prepares the patient for expected symptoms and sensations, and dialogue and shared reflections facilitate strategies for coping with symptoms and experiences associated with the condition, for example when leg pain is part of the treatment for getting better. The group education is a two-hour-long session, about the pathophysiology of IC, medications, health behaviour, disease management, quality of life, and coping with the disease. The principal investigator (MS), who is an experienced cardiac rehabilitation nurse with specific knowledge of IC to ensure protocol compliance, will perform the intervention. Information given will also be based on national guidelines and standard treatment of patients with IC. A clinical dietician will advise participants in a two-hour-long group session about healthy diet and atherosclerosis, and in addition give access to individual consultation.

Albert Bandura’s Social Cognitive-Behavioral Theory and self-efficacy inspires the intervention. Its focus is on the dynamic interaction of person and behaviour; the individual’s actual ability to perform the appropriate behaviour; learning a new skill or knowledge by observing others; external responses to the individual’s behaviour that either encourage or discourage the behaviour expectations: the anticipated consequences of a behaviour; and self-efficacy: the person’s confidence in his or her ability to perform a behaviour [27, 30]. Consequently, the individual, the group, spouses, and surroundings in a rehabilitation setting are important. Spouses are therefore invited to participate in group sessions as well as in individual sessions.

Studies show that text messages can facilitate lifestyle changes [31–33]. After completion of exercise training, participants are offered personalised motivational follow-up text messages. The content, frequency, and duration of the text messages are agreed upon individually for the next 8 months and will be reassessed at follow-ups after 3 and 6 months.

### Outcomes and data collection

Data will be collected at admission, discharge, 6 months and 12 months administrated by the primary investigator (see Table 1). The primary and the secondary outcomes reflect the primary modifiable factors of the intervention, and a number of explorative outcomes will be collected to evaluate the effect and meaning of the intervention (see Table 2). The post-discharge experiences of patients in the intervention group will be explored through semi-structured qualitative interviews. Patient flow is illustrated in Fig. 1.

**Table 1 Tab1:** The CIPIC Rehab Study - exploratory quantities subjected to post hoc analysis

Quantity	Time of measure	Type of quantity
Demographic		
Sex	Baseline	Binary (M/F)
Age, height, weight, body mass index (BMI)	Baseline	Continuous
Marital, occupational, educational status	Baseline	Categorical
Clinical		
Charlson Comorbidity Index [34]	Baseline, 6, 12	Categorical
Hypertension	Baseline 6, 12	Binary (Y/N)
Smoking+ Fagerströms test, (Alcohol Timeline Followback)	Baseline, 6, 12	Categorical
Medication (routine drugs; antiplatelet; statins and other medication)	Baseline, 6, 12	Categorical
Nutritional screening ‘HjerteKost’: fat-fish-fruit-green score [35]	Baseline, 6, 12	Categorical
Paraclinical		
Blood work (biomarkers, cholesterol, HBa1C, Hg, thyroid)	Baseline, 6, 12	Continuous
Physical function		
The standardised treadmill walking test [36, 37]	Baseline, 6, 12	Continuous
Six-minute walking test (before and after supervised exercise training) [38]	Baseline, 3	Continuous
Sit to stand test (before and after supervised exercise training) [39]	Baseline, 3	Continuous
Level of physical activity (0–7 times a week)	Baseline, 6, 12	Categorical
Questionnaires		
HADS, Hospital Anxiety and Depression Scale [40]	Baseline, 6, 12	Categorical
VascuQol, Vascular Quality of Life questionnaire [41]	Baseline, 6, 12	Categorical
PAM13, 13-item Patient Activation Measure [42]	Baseline, 6, 12	Categorical
Pedometer, text message (intervention group)	3 months, 6	Binary (Y/N)
Participation in dietician and nurse session (intervention group)	3 months	Binary (Y/N)

*M/F* male/female, *Y/N* yes/no

**Table 2 Tab2:** Focus group - interview topics

Supervised exercise training: physiotherapist. Content and education	
Education session: nurse and dietician. Content and education	
Patients’ experiences of participating in the intervention group.	
Knowledge and uncertainty about IC	
Experiences of factors and barrier that supported or hindered adherence to the intervention.	
Factors that influence coping strategy, persistent lifestyle changes	
Importance of environment and togetherness with similar patients	
Empathy, support and motivation	
Risk factor management	
Coping behaviours	
Change interventions	
Attitudes, beliefs, how to handle the pain	
Feeling better mentally	
Accessibility and compliance	
Self-monitoring goal setting	
Exercise logbook and pedometers. Motivational text message.	
Specific walking advice to promote self-managed walking	
Quality of life	
Solution behaviour change techniques	
Patient satisfaction of participate in the IC rehabilitation programme and point out if any suggestions for changes.

**Fig. 1. Fig1:**
[figure not shown]
Patient flow

### Primary outcome

MWD will be measured by the standardised treadmill walking test based on a graded protocol (3.2 km/hour with 2% increase every 2 minutes). Treadmill assessment has the highest reliability when using a graded protocol together with outcome measurements, such as initial claudication distance and absolute claudication distance. Results of treadmill testing are expressed as the initial claudication distance, the moment claudication pain begins and the absolute claudication distance, the moment the test has to stop due to the maximal level of bearable claudication pain [36, 37]. The follow-up treadmill walking test will be performed by a research assistant blinded as to the patients’ group affiliations.

### Secondary outcome

PWD will be measured by the standardised treadmill walking test as described above and with a numeric rating scale for pain [37, 43]. Daily physical activity is measured by self-reported number of times per week of walking or physical exercise activity of at least 30 minutes, as recommended by the National Board of Health [44]. Diet will be measured by a diet questionnaire (HjerteKost), a validated Danish instrument with 19 items. The scale offers two scores, a fat and a fish-fruit-green score, each of which can range from 0 to 18. To be able to achieve the term ‘healthy’ the score must be at least 75% in both the fat and the green scores [35]. The instrument is validated and recommended by the National Board of Health [28].

### Exploratory outcomes

Smoking is measured by self-reported smoking behaviour by the Fagerström Test for Nicotine Dependence. The self-administered questionnaire has good internal validity and a good correlation with nicotine levels as an instrument for measuring addiction to tobacco [45]. Alcohol consumption will be measured by the Alcohol Timeline Followback (TLFB). TLFB has been shown to be a psychometrically sound assessment instrument for obtaining retrospective daily estimates of alcohol consumption. TLFB has been extensively evaluated in various settings, over varying reporting intervals and with diverse drinker populations and has been found to have very good measurement properties [46, 47].

### The Hospital Anxiety and Depression Scale (HADS)

HADS is a 14-item instrument that measures symptoms of anxiety (HADS-A) and depression (HADS-D). The scale offers two subscales, each of which can range from 0 to 21. Scores of 0–7 for either subscale are regarded as normal; 8–10 suggest the presence of a mood disorder; and 11 and above suggest the probable presence of a mood disorder. This tool has been translated and validated in many countries and its capacity to detect anxiety and depressive disorders is widely recognised [48].

### The Vascular Quality of Life questionnaire (VascuQoL)

VascuQoL (VQ6) is a PAD-specific instrument recommended as one of the preferred questionnaires when evaluating quality of life outcomes in patients with PAD. The VQ6 is a six-item questionnaire, developed using a combination of qualitative and quantitative methodology. The VQ6 has acceptable to good psychometric properties regarding data quality, scale assumptions, targeting, validity and reliability. Further, VQ6 seems to be easy to use and comprehend within the target population of patients with PAD [41].

### The Patient Activation Measure (PAM)

PAM-13 is a 13-item instrument for evaluating educational interventions aimed at improving patient engagement. Patient activation specifies the level of patients’ engagement and may contribute to better self-management, higher engagement in treatment and greater patient satisfaction. The European translations of PAM-13 resulted in four instruments with good psychometric capabilities for measuring patient activation. All items have five possible responses with scores ranging from 0 to 4: (1) disagree strongly, (2) disagree, (3) agree, (4) agree strongly or (0) not applicable [42, 49].

## Complementary studies

Numerous data will be collected to evaluate the effect and meaning of the intervention.

### Quantitative data

The quantitative study consists of an individual questionnaire survey conducted as interview by the principal investigator. The survey including data about feasibility: participation (number of times), use of pedometer (yes/no), logbook (yes/no) and to what extent it has motivated daily physical exercise, exercise choice after the course, and text messages (yes/no). Results from the physiotherapist six-minute walking test and 30-second chair stand test, before and after in metres/number are also included.

### Qualitative explorative data

As a part of the study, brief individual interviews exploring course satisfaction, suggestions for changes, and the relevancy of the various rehabilitation components will be conducted. Furthermore, focus group interviews of patients participating in the intervention group will also be conducted. Prior to interviewing, an interview guide will be developed. It will be used to help explore patient experiences of training and teaching sessions, factors helping or hindering improvement in health behaviour, the use of the pedometer, logbook, and text message influenced motivation/adherence, patient satisfaction with the intervention and suggestions for future rehabilitation programmes. Research questions will be developed using knowledge from existing qualitative studies in the field and the individual brief interviews [6, 7, 9, 15, 17, 50, 51] (see Table 2). The focus group interviews will be conducted by the principal investigator (MS) and two assistant moderators that register key points and takes field notes [52]. Patients will be recruited during their 3- and 6-month follow-ups at the Healthcare Centre or at the Department of Vascular Surgery as a convenience sampling with consecutive recruitment of participants according to the groups in which they exercised during the training sessions. To embrace the potential impact of any team spirit developed during the training session, we consider focus groups and recruitment of participants according to training groups to be relevant. The interviews will be held in well-known surroundings in the Healthcare Centre. The size of the focus groups will be five to eight participants to secure an opportunity for each person to share insights, experiences and observations. Smaller groups allow more in-depth conversation and afford each person a greater opportunity to speak. ‘Information power’ will guide the adequate sample size and the number of focus group interviews [52].

### Data collection and data analysis

The interviews will be audio recorded and transcribed verbatim. Interviews are anticipated to last approximately one hour. Thematic analysis according to Braun & Clarke will be used to analyse data [53]. This means combining a coding analysis with the content of the focus group discussion [11, 13]. Derivation of themes will be identified by an exploratory analysis to present selected patterns relevant for the study aim and collected data. Numbers of data coders, description of the coding tree, software program, illustrated themes/findings, quotation identification, consistency between the data presented and the findings, as well as the clarity of major and minor findings will be a part of the analysis [54, 55]. The thematic analysis will be used as a systematic approach to the analysis of quality data from the focus group interviews. That involves identifying themes or patterns of meaning by coding and classifying data textually, according to themes and interpreting the resulting thematic structures by seeking commonalties, relationships, overarching patterns, theoretical constructs, or explanatory principles [56].

## Statistical analysis

A trial-independent statistician will make a blind analysis of the data and the primary and secondary analyses will be performed according to the intention-to-treat principle. We will use general regression models for the continuous outcomes and logistic regression models for binary outcomes. In the analysis of the primary outcome, the outcome (MWD at 6 months) will be analysed with adjustment for baseline MWD, sex or age (included continuously). For the three secondary outcomes – PWD distance, level of physical activity and diet at 6 months – the analysis will be done similarly with adjustment for baseline values, sex and age (continuous). As exploratory analyses of MWD, PWD, smoking behaviour, diet and patient-related outcome measures, mixed general and generalised models with repeated measurements will be used including measurements at baseline, 6 and 12 months in the same model. These models will also be used for all other explorative outcomes. In these models, the interaction between intervention group and time is of primary interest, indicating different developments after intervention start. In the case of significant results in the primary outcome, sensitivity analyses will be performed to estimate the potential effect of data missing at random by a worst-case scenario. Let X be the group where a beneficial effect is observed, and Y be the other group. Missing values in group X will be imputed by the minimum value found in the material and missing values in group Y will be imputed by the maximum value found. The primary outcome will be tested first using a significance level of 0.05. Analyses of the secondary and exploratory outcome measures as planned above will be analyzed with no *p* value adjustment due to multiplicity. Instead, the interpretation of these results will be assessed in the light of multiple testing, i.e. statistically significant effects will be interpreted in the context of increased risk of type I error. The clinical effect size will be reported by Cohen’s d. Per protocol analyses of the primary and secondary outcomes will be performed.

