### Sample size and power calculation

The expected average baseline value of MWD has been set to 120 m with a detected 50% improvement (60 m). There is a wide variance in MWD in this patient group and consequently the standard deviation (SD) is set at 100 m, based on an expected improvement in walking ability of approximately 50% to 200% [18]. With a 5% significance level and 80% power, it will thus be necessary to include 88 patients to detect an improvement of 60 m in MWD in the intervention group at the 12-month follow-ups, compared with the control group. Owing to the previously mentioned risk of co-morbidities, combined with an expected drop-out, a drop-out of 25% must be expected, therefore the investigators plan to include 118 patients in total (59 in each group).

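### The exploratory mixed models do not fix a common baseline mean; on the usual reading they give change-score contrasts, no more precise and usually less precise than the plan's own baseline adjustment

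*Protocol article*

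**What the plan says.** The Statistical analysis section of the protocol article plans two kinds of model.

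- **Primary and secondary outcomes, 6 months only.** These are regressions adjusted for baseline. For the primary outcome the text is "the outcome (MWD at 6 months) will be analysed with adjustment for baseline MWD, sex or age (included continuously"). The three secondary outcomes are handled in the same way.
- **Exploratory analyses.** These are mixed general and generalised models "including measurements at baseline, 6 and 12 months in the same model". Of these it says: "In these models, the interaction between intervention group and time is of primary interest, indicating different developments after intervention start".

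For the second kind, the section does not state whether the group means at baseline are free or held equal, does not make baseline a covariate, and names no covariance structure. Study procedure puts baseline data collection before randomisation. Sample size and power calculation sizes the trial "to detect an improvement of 60 m in MWD in the intervention group at the 12-month follow-ups, compared with the control group".

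**The concern.** Because baseline is measured before randomisation, any difference between arms at baseline is chance and its true value is zero. A model with group, time and group-by-time terms and free baseline means estimates that difference anyway and subtracts it from the follow-up difference. Each visit's interaction contrast then becomes a difference in changes from baseline. The 6-month regressions adjust for baseline instead, which under randomisation is at least as precise.

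What is at stake is the width of confidence intervals, not validity. The mixed models are nevertheless the only analysis the article describes at 12 months, which is the time point in the sample-size statement. They are also the only analysis it describes for VascuQoL, HADS and PAM. Study objectives states hypotheses at both 6 and 12 months, so precise arm differences at each visit are what the reader will want from these models.

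**Working it through.** **Inputs from the article.** Difference 60 m, SD 100 m ("the standard deviation (SD) is set at 100 m"), 5% significance level, 80% power, 1:1 allocation, 118 patients (59 per arm), and "a drop-out of 25% must be expected".

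**Assumed.** The correlation ρ between baseline and follow-up, shown from 0.4 to 0.7. The article gives no ρ. It also gives a single SD, so the ratio k of follow-up SD to baseline SD is varied too.

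**Step 1: the plan's own figure.** n per arm = 2 × (1.96 + 0.84)² × 100² / 60² = 43.6, rounded up to 44, so 88 in total. Then 88 / 0.75 = 117.3, rounded up to 118. Both stated numbers reproduce with a two-sided test. This calculation compares two means and uses no baseline information, so it does not itself settle which repeated-measures model is meant.

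**Step 2: variances, complete data, equal SDs (σ), n per arm.**

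- Free baseline means (change score): 2σ²(1 − ρ) × 2/n
- Common baseline mean, or baseline as covariate: σ²(1 − ρ²) × 2/n
- Variance ratio: 2/(1 + ρ)
- Information lost: 1 − (1 + ρ)/2 = (1 − ρ)/2

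A generalised least squares calculation for three visits with saturated means confirms both variances. At ρ = 0.5 with 59 per arm, in units of σ², the free model gives 0.0339, identical to the change score. The common-baseline model gives 0.0254, identical to the baseline-adjusted regression.

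**Step 3: numbers for 44 per arm, SD 100 m, 60 m.**

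| ρ (assumed) | SE free | SE common baseline | Information lost | Power free | Power common baseline |
|---|---|---|---|---|---|
| 0.4 | 23.4 m | 19.5 m | 30% | 72.9% | 86.7% |
| 0.5 | 21.3 m | 18.5 m | 25% | 80.4% | 90.1% |
| 0.6 | 19.1 m | 17.1 m | 20% | 88.2% | 94.0% |
| 0.7 | 16.5 m | 15.2 m | 15% | 95.3% | 97.6% |

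At ρ = 0.5 the free-baseline interval is about 15% wider (21.3/18.5). At ρ = 0.7 it is about 9% wider (16.5/15.2).

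**Step 4: the planned drop-out.** Take 59 per arm, 25% without follow-up data and equal correlations between visits. Patients with a baseline only now contribute to the free model, so it is no longer exactly a change score: at ρ = 0.5 its variance is 0.0424, against 0.0452 for the completers' change score and 0.0339 for the common-baseline model. The loss becomes 24%, 20%, 16% and 12% for ρ = 0.4, 0.5, 0.6 and 0.7. If instead 12.5% are lost by 6 months and 25% by 12 months, the 12-month loss is almost the same: 24.5%, 20.3%, 16.1% and 11.9%.

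**Step 5: unequal SDs, complete data.** The loss is 1 − k²(1 − ρ²)/(1 + k² − 2ρk), which equals (1 − ρk)²/(1 + k² − 2ρk). It is never negative and is zero when ρk = 1.

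| k | ρ = 0.4 | 0.5 | 0.6 | 0.7 |
|---|---|---|---|---|
| 1 | 30% | 25% | 20% | 15% |
| 1.25 | 16% | 11% | 6% | 2% |
| 1.5 | 8% | 4% | 1% | 0% |

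A larger k does not always shrink the loss: at k = 2 it is 0% for ρ = 0.5 but 20% for ρ = 0.8.

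**The case against.** The strongest reply is that the article never says the baseline means are free. A model with one common baseline mean also carries group-by-time terms after baseline, and the wording about developments after the start of the intervention fits it. Parameterisation and covariance structure are commonly left to a full protocol or SAP, and neither is shown. This stands in part: a reader might infer that the plan commits to an unconstrained model, but the text is silent. Free means are still the ordinary reading, the more so because the same section states baseline adjustment outright for the 6-month regressions and not here.

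Several stronger readings are also not supported:

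- **A loss of 15% to 30% as a property of this plan.** That range needs ρ of 0.4 to 0.7, equal SDs and complete data. A larger follow-up SD is credible, since the sample-size section expects improvements ranging from about 50% to 200%.
- **Reporting only an overall interaction test.** Over three visits such a test has two degrees of freedom and does not locate the effect. The article does not say that visit-specific differences will be omitted.
- **A threat to the main results.** The affected models are labelled exploratory, the Discussion promises caution with them, and their estimates stay unbiased.
- **The same factor for binary or categorical outcomes.** The algebra holds for continuous outcomes and does not transfer directly to the generalised models.
- **A fix that makes the two 6-month MWD estimates agree.** They could still differ under drop-out, because the mixed model also uses 12-month data and the regression has covariates not stated for the mixed model.

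The mismatch between a 6-month primary analysis and a 12-month sample-size statement is a separate matter and does not raise the severity here.

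**Conclusion.** The point holds as a low-severity matter of precision. The article leaves the baseline means unconstrained in its wording, and under the usual reading the visit contrasts for continuous outcomes are unbiased but never more precise than the baseline adjustment the plan itself uses at 6 months. The direction of the loss is certain under that reading; its size depends on values the article does not give. Over the cases worked here it runs from 30% of the information down to practically nothing. The smallest values arise where ρ times the SD ratio is close to 1. If a common baseline mean is in fact intended, nothing is lost and only the wording needs attention.

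**What to change.** For continuous outcomes in the exploratory mixed models, state that both arms share one baseline mean (no group term at baseline) with an unstructured covariance across the three visits. Equivalently for this purpose, use baseline as a covariate with 6 and 12 months as the responses. Report the arm difference at 6 and at 12 months, each with a 95% CI. For the generalised models, adjust for the baseline value as a covariate, without claiming the same gain in efficiency.

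The cost is a sentence or two in the analysis plan and one fewer parameter in the common-mean model. No extra data or patients are needed, and the primary and secondary 6-month analyses stay as they are. The choice should be recorded before the arm comparisons are seen.

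### The missing-data sensitivity analysis is described as missing at random but is an extreme min/max bound, and at the planned 25% drop-out it overturns practically every true 60 m benefit

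*Protocol article*

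**What the plan says.** The Statistical analysis section regresses MWD at 6 months on group with adjustment for baseline MWD, under the intention-to-treat principle. If the primary result is significant, "sensitivity analyses will be performed to estimate the potential effect of data missing at random by a worst-case scenario". The rule follows. X is the group with the observed benefit and Y the other group. "Missing values in group X will be imputed by the minimum value found in the material", while missing values in Y take the maximum found.

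The same section plans exploratory mixed models for MWD and other outcomes, with baseline, 6 and 12 months in one model and the group-by-time interaction as the main interest. It does not mention missing data in connection with them.

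Under Sample size and power calculation, "the standard deviation (SD) is set at 100 m", the target is "to detect an improvement of 60 m in MWD in the intervention group at the 12-month follow-ups" compared with control, and "a drop-out of 25% must be expected".

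**The concern.** The description and the rule contradict each other. Under missing at random, the unseen values resemble those of observed patients with the same recorded history. Giving every missing patient in the better arm the lowest value in the data, and every missing patient in the other arm the highest, assumes that the reason for missingness is tied to the unseen value as unfavourably as the data allow, and in opposite directions by arm.

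Two consequences follow. First, with a quarter of patients missing, the imputed extremes may swamp any realistic effect, so that the analysis gives the same answer for robust and fragile results. A trial that succeeds as designed would then publish a real benefit beside a prespecified check pointing towards harm. Second, because the analysis is triggered by significance, it does not examine whether drop-out contributed to a null result.

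**Working it through.** **Inputs from the documents.** Difference 60 m, SD 100 m, 5% significance (taken as two-sided, which reproduces the stated size), 80% power, 88 evaluable, 25% drop-out, 118 randomised, 59 per arm.

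**Reproducing the plan's figure.** n per arm = 2 × (1.96 + 0.84)² × 100² / 60² = 43.6, so 44 per arm and 88 in total. 88 / 0.75 = 117.3, so 118. The stated figures hold. They imply about 44 observed and 15 missing per arm.

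**The imputed difference.** With equal losses and R = maximum minus minimum of the observed MWD values, the unadjusted worst-case difference is

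60 × (44/59) − (15/59) × R.

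It is negative once R exceeds 60 × 44 / 15 = 176 m. A sample of 44 values with SD 100 m must have a range of at least 2 × 100 × √(43/44) = 198 m, whatever its distribution. So if the trial observes a 60 m difference, an SD of 100 m and even losses of 25%, the unadjusted estimate must change sign.

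**How large the reversal is.** The documents give no observed minimum or maximum, so R is an assumption. With a fraction d missing, the difference is 60(1 − d) − dR. At d = 0.25:

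- R = 350 m: 45 − 87.5 = −42.5 m
- R = 500 m: 45 − 125 = −80 m

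The difference is zero at d = 60 / (60 + R):

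- R = 300 m: 16.7%
- R = 400 m: 13.0%
- R = 500 m: 10.7%
- R = 600 m: 9.1%

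All lie below 25%. In the simulations described next, R averaged about 410 to 550 m at 25% missing.

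**Simulation of the stated procedure.** Settings: 59 per arm, means 120 and 180 m, SD 100 m, and equal numbers removed at random per arm. The complete cases were fitted by baseline-adjusted regression. Where the benefit was significant, the min/max rule was applied and the model refitted. Assumed: four distributions (normal, normal floored at 0, gamma, lognormal), baseline correlation 0 or 0.6, and 1,500 to 2,000 trials per setting.

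| Missing per arm | Significant benefits that stay significant | Sign reversed | Mean worst-case difference |
|---|---|---|---|
| 1 (about 2%) | 79–92% | 0% | +49 to +55 m |
| 3 (5%) | 25–47% | 0–4% | +29 to +36 m |
| 6 (10%) | 0.2–2.3% | 20–49% | −2 to +12 m |
| 9 (15%) | 0% | 80–97% | −34 to −11 m |
| 15 (25%) | 0% | 100% | −93 to −57 m |

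At 25% missing, 73 to 98% of the significant benefits become significant in favour of control.

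**Larger true effects, 25% missing** (floored normal and gamma, correlation 0.6). The sign reverses in 99.6 to 100% of trials at 100 m, 86 to 88% at 150 m, 30 to 43% at 200 m and 5 to 14% at 240 m. At most 0.5% stay significant even at 240 m. Over a wider set of distributional assumptions, the reversal at 240 m ran from 3 to 35%. At 10% missing and 240 m, nearly all significant results survive.

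**The case against.** **The mixed model exists.** It can use patients with incomplete MWD under missing at random, so a reader who infers that the plan has no plausible analysis of incomplete data goes too far. This stands. What remains is that the model is exploratory, centres on the group-by-time interaction, and is not put forward as support for the 6-month result.

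**The article is a condensed document.** Further missing-data analyses may sit in a full protocol or SAP that is not shown, so it cannot be said that plausible departures from missing at random are never assessed. Nor does the article say outright that the primary regression is complete-case. Both points stand. The finding rests on what the article states: a wrong description and a rule whose result follows from the plan's own inputs.

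**It is already called a worst case, and such bounds are legitimate.** True, and as a stress test of a positive claim the significance trigger has a rationale. But the same sentence says missing at random, and a bound that practically no true 60 m benefit can pass is not a useful stress test.

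**The bound does not show harm whatever the truth.** A reader might infer this from the 25% row, and the documents do not support it. The sample size section speaks of improvements of about 50% to 200%, or 60 to 240 m on 120 m. At 240 m the worst-case estimate usually still favours the intervention.

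**The 25% is stated beside a 12-month power calculation, while the primary analysis is at 6 months.** Loss at 6 months may be smaller. At 10% missing, 54 − (41 to 55) gives −1 to +13 m for R of 550 to 410 m: near zero, not harm. Significance is nevertheless almost always lost there.

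**Conclusion.** Wrong as written; should-fix. The description as missing at random is an error that can be read off the text. At the plan's own effect, SD, size and drop-out, the bound cannot separate robust from fragile results: 0% of true positives stay significant and the sign reverses. At 10% missing about 0 to 3% stay significant. It is informative to some degree at about 5% missing or less, or when the true effect is far above 60 m.

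The simulated figures assume equal losses at random in both arms and the four distributions listed. The unadjusted sign reversal at 25% needs only the planned difference, SD and even losses. One might infer that the primary conclusion is at risk, but the plan gives no rule by which a sensitivity result overrides the test: "The primary outcome will be tested first using a significance level of 0.05". Sample size and data collection are also unaffected, so this is not a must-fix.

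**What to change.** 1. Delete the missing-at-random wording from the description, and keep the min/max imputation only as a labelled outer bound.
2. Whatever the primary p value, run a missing-at-random analysis of 6-month MWD. Use either the 6-month contrast from the mixed model already planned, or multiple imputation by arm with baseline MWD, age, sex and 12-month MWD.
3. Add a delta-adjusted tipping-point analysis: shift imputed intervention values down in fixed steps (20 m, for example) and report the shift at which significance is lost.

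Cost: a wording change and some programming. No new data.
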